### 1.3.6 Rational for study medication

Two mTOR inhibitors are available for the treatment of TSC, sirolimus and everolimus. These two medications differ only by one additional ethylester group in everolimus, resulting in differences in their half-lives, solubility, elimination, interindividual tolerability and efficacy. Everolimus is currently approved for the treatment of most TSC-manifestations, including the treatment of SEGAs for all age groups, mostly because Novartis Pharmaceuticals, that developed everolimus, supported the key clinical studies leading to approval by the FDA and EMA [38]. Similar trials with sirolimus failed due to lack of funding and the only approved indication for sirolimus is spontaneous pulmonary lymphangioleiomyomatosis due to proposed somatic mutation of TSC [39]. Direct head-to-head clinical trials comparing both medications in TSC are not available and most authors treating older children and adults, currently prefer everolimus, due to the more robust clinical trial experience [40]. However, sirolimus holds a key advantage over everolimus, in that it is available as oral solution (Rapamune®) facilitating the careful administration of precise doses in neonates and infants. Everolimus, by contrast, is only available as tablet with limited solubility in water, which renders precise dosing difficult and bears higher potential risk of accidental application of inaccurately low or high doses. In addition, sirolimus and everolimus work in a similar fashion, and are considered equally effective and interchangeable by leading TSC experts (reviewed in detail by Franz *et al.* [41]), supported by recent evidence of equal tolerability and efficacy of sirolimus in TSC-related seizures [36, 42]. Furthermore, due to the significant higher cost for everolimus for this publicly funded trial, the investigators favor the use of sirolimus.

### 1.3.7 Safety of sirolimus in neonates and young infants

#### 1.3.7.1 Systematic research for evidence synthesis

To obtain a full synthesis of the available evidence for the risk and side effects, as well as long-term effects of Sirolimus in infancy and early childhood, we conducted a systematic literature review. The databases MEDLINE via PubMed, CENTRAL via Cochrane Library and Embase were searched for reviews and clinical trials on January 15, 2023.

##### Search terms:

#1 sirolimus/  
#2 rapamune/  
#3 mammalian target of rapamycin inhibitor/  
#4 OR/1-3  
#5 risk assessment\*/  
#5 safety/  
#6 adverse event\*/  
#7 long term outcome\*/  
#8 OR/5-7  
#9 AND/4,8

##### Filters:

#10 cochrane review  
#11 controlled clinical trial  
#12 review  
#13 systematic review  
#14 randomized controlled trial  
#15 meta-analysis  
#16 OR/10-15  
#17 embryo  
#18 fetus  
#19 infant  
#20 newborn  
#21 preschool  
#22 OR/17-21  
#23 [2000-2023]/py)  
#24 AND/23

Figure 1: PRISMA Search Process

The following PRISMA 2009 Flow-diagram summarizes the search process [43]:

[figure not shown]

Reports of mTOR inhibitor therapy in neonates with TSC predominantly focus on the treatment of cardiac rhabdomyomas, however raise no major safety concerns (summarized in [28]). Due to the absence of safety and exploratory studies on mTOR inhibitors in infants and young children, these therapies are usually prescribed off-label [44]. To address this issue, we recently published data on the safety and efficacy of mTOR inhibitor treatment in 17 young children with TSC under 2 years. Treatment was well tolerated and most adverse events (AEs), rated by the *Common Terminology Criteria of Adverse Events (CTCAE, current Version)* were limited to mild (grade 1) and moderate (Grade 2). Adverse events included mild transient stomatitis (2 cases), worsening of infantile acne (1 case), increases of serum cholesterol and triglycerides (4 cases), changes in serum phosphate levels (2 cases), increase of cholinesterase (2 cases), transient neutropenia (2 cases), transient anemia (1 case), transient lymphopenia (1 case) and recurrent infections (7 cases). No grade 3-4 adverse events were reported [28]. In a study of 45 infants reported by Krueger and colleagues, 7 patients experienced severe (grade 3) AEs, including ulcers/stomatitis (N = 1), upper respiratory tract infections (N = 2), gastroenteritis (N = 1), other infections (N = 1), abnormal complete blood count (N = 1) and elevated cholesterol (N = 1). No life-threatening (grade 4) AEs or death/disability (grade 5) were reported in either study [27]. A recent two-center retrospective data analysis of medical records of individuals with TSC who were started on sirolimus under the age of two years, reported at least one adverse event in all participants (n=21, median age at onset of sirolimus 104 days). The majority of adverse events were graded as 1 and 2 according to the CTCAE. No adverse events grade 4 or higher were reported. In all patients, sirolimus was administered once a day as oral solution (Rapamune® 1 mg/mL). Initial doses were calculated to be 0.5 mg/m^2/day and varied from 0.01 to 0.07 mg/kg/day. Dosing was adjusted according to sirolimus plasma levels. Trough levels were targeted to range between 3–4 ng/mL, with median plasma levels throughout the study of 4.34 ng/mL (0.79–13.89 ng/mL). The most prevalent AEs were anaemia, thrombocytosis, and hyperlipidemia (see [Table 2](#)). Infections and mouth ulcerations, often reported in older patients, were infrequent and of mild or moderate grade. The authors concluded, that adverse effects associated with sirolimus use in infants and young children with TSC are frequent yet not life- or health-threatening. [45]

**Table 2: Sirolimus adverse effects depending on age [45]**

| Adverse Effect   Age | 0–6 Months         | 6–12 Months   | 12–24 Months  | 24–36 Months |
|----------------------|--------------------|---------------|---------------|--------------|
|                      | N  (%) | N (%)         | N (%)         | N (%)        |
| Hyperlipidemia       | 10/12 (83.33)      | 11/13 (84.62) | 13/13 (100)   | 5/8 (62.5)   |
| Hypercholesterolemia | 8/12 (66.67)       | 5/12 (41.67)  | 8/13 (61.54)  | 3/8 (37.5)   |
| Elevated LDL         | 5/11 (45.45)       | 5/12 (41.67)  | 7/13 (53.85)  | 2/7 (28.57)  |
| Hypertriglyceridemia | 7/12 (58.33)       | 8/12 (66.67)  | 10/13 (76.92) | 3/7 (42.86)  |
| Anemia               | 11/12 (91.67)      | 8/14 (57.14)  | 9/14 (64.29)  | 5/10 (50)    |
| Thrombocytosis       | 7/12 (58.33)       | 5/14 (35.71)  | 11/14 (78.57) | 7/10 (70)    |
| Neutropenia          | 5/12 (41.67)       | 3/14 (21.43)  | 5/14 (35.71)  | 1/10 (10)    |
| Elevated D-dimers    | 2/2 (100)          | 0/1 (0)       | 1/2 (50)      | 0/0 (0)      |
| Elevated bilirubin   | 3/7 (42.86)        | 0/4 (0)       | 0/4 (0)       | 1/6 (16.67)  |
| Low ALT              | 4/12 (33.33)       | 4/13 (30.77)  | 6/12 (50)     | 4/7 (57.14)  |
| Elevated AST         | 2/12 (16.67)       | 1/13 (7.69)   | 4/12 (25)     | 2/7 (28.57)  |
| Elevated fibrinogen  | 0/6 (0)            | 1/2 (50)      | 1/3 (33.33)   | 0/1 (0)      |
| Infections           | 2/12 (16.67)       | 3/13 (23.08)  | 5/13 (38.46)  | 5/10 (50)    |
| Mouth ulcers         | 2/11 (18.18)       | 0/14 (0)      | 0/13 (0)      | 1/10 (10)    |

 N—number of patients who reported the adverse effect divided by the number of patients who were tested for the adverse effect.

|                                                                    |                                              |                                |
|--------------------------------------------------------------------|----------------------------------------------|--------------------------------|
| Clinical Trial Code: PROTECT
EU trial number: 2022-502332-39-00 | Trial Protocol
(Version 06; (01.10.2024)) | Page 32 of 110
CONFIDENTIAL |
|--------------------------------------------------------------------|----------------------------------------------|--------------------------------|

Along these lines, Overwater and colleagues conducted a clinical trial investigating whether sirolimus can reduce seizure frequency in children and infants with TSC [42]. The trial showed potential beneficial effects on seizure reduction, however, likely due to the small number of children enrolled (N = 23), failed to reach significance. No changes in cognitive development were observed, however, the youngest child enrolled was 1.8 years old, and most children already suffered from severe intellectual disability at the time of inclusion, thus likely limiting therapeutic effects. All patients in this trial reported at least one AE, most commonly upper respiratory tract infections, gastrointestinal problems and acne-like lesions. Severe AEs occurred in 5 patients, including aphthous ulcers (N = 2), pneumonia requiring hospitalization, upper respiratory tract infection and increase in seizure frequency, thus requiring discontinuation of treatment in these 5 cases. Further evidence for the use of mTOR inhibitors in young children comes from He *et al.*, who evaluated the effect of sirolimus on reduction of seizure frequency in 91 TSC-patients between 2 months and 11.3 years (median 21.2 months), reporting the highest response rates within the first 2 years of life, thus supporting the hypothesis that early initiation of mTOR inhibitor treatment yields the highest benefit [36].

For further information to the excipients and their potential adverse effects of Rapamune® (contains up to 25 mg ethanol and 350 mg propylene glycol (PG; E1520) per ml), see chapter 5.2.2.7.

### 1.3.8 Long-term tolerability of sirolimus in neonates and young infants

Information on the tolerability and long-term effects of sirolimus on growth, development, and maturation of relevant organ systems in this young age group is limited. Maria *et al.* presented data of a 5-year follow-up study of 22 children with hyperinsulinemic hypoglycaemia (CHI) with a median age at start of sirolimus treatment of 3.87 months and a median starting dose of 0.96 mg/m^2/d [46]. Side effects of treatment occurred in 86.4% with a median delay of 13 months (range 1-52). Infections were most commonly reported (17/22). No growth disturbances or failure to thrive were observed. A review of the off-label use of sirolimus and everolimus in 101 published reports of diverse indications, including 255 children with TSC treated with sirolimus at a median dose of 3.6 mg/m^2/d, did not report relevant long-term use complications of treatment [44]. The experience with sirolimus in kidney transplant patients shows a good overall safety profile and was associated with a lower risk of developing malignancies compared to other immunosuppressants [47]. A retrospective, multicenter chart review of severe adverse events (SAE) associated to sirolimus “off-label” therapy for vascular anomalies identified 17 SAEs in 14 patients. The age at initiation of sirolimus therapy was under 2 years (n = 5), 2–6 years (n = 5), and older than 12 years (n = 4). SAEs occurred during the first 3 months of therapy (n = 7), between 3 and 12 months (n = 7) and after 1 year of therapy (n = 3). The most frequent SAE was viral pneumonia (n = 8) resulting in one death due to a metapneumovirus infection in a 3-month-old child and a generalized adenovirus infection in a 28-month-old child. Sirolimus blood level at the time of SAEs ranged between 2.7 and 21 ng/L [32]. In a study of pediatric liver transplant recipients (n=50) under therapy with everolimus in combination with reduced tacrolimus or cyclosporine A, most male patients (87.5%) had testosterone levels below normal range. This was not associated to changes in height or weight percentiles. Among patients available for Tanner staging after 12 months of therapy, all patients aged <8 years belonged to Tanner stages 1 or 2. No events of abnormal sexual maturation were reported during the study period. Although limited by sample size, these findings indicate that combination of mTOR inhibitors such as everolimus with tacrolimus or cyclosporine A does not appear to negatively impact linear growth or sexual maturation in pediatric liver transplant recipients up to 12 months post treatment initiation [48]. Other clinical data on potential adverse effects on longitudinal growth in renal transplant recipients is inconclusive [49, 50], and information on the effects of low-dose treatments with sirolimus on organ development and growth is lacking. Given the lack of data, we additionally assessed available information from

|                                                                    |                                              |                                |
|--------------------------------------------------------------------|----------------------------------------------|--------------------------------|
| Clinical Trial Code: PROTECT
EU trial number: 2022-502332-39-00 | Trial Protocol
(Version 06; (01.10.2024)) | Page 33 of 110
CONFIDENTIAL |
|--------------------------------------------------------------------|----------------------------------------------|--------------------------------|

our previously published cohort of early treated infants and children (Saffari et al 2019). We analysed available novel data on growth (height, weight) and also on cardiac function (data from original echocardiographies with markers for hypertrophy and ejection fraction) and compared it to controls. Considering the limitation from the small sample size, we were not able to identify specific safety concerns in our cohort for effects on growth parameters or cardiac function (personal data).

The TOSCA-PASS registry as a post authorization safety study to document the long-term safety and tolerability of everolimus (as similar mTOR inhibitor with a comparable profile) provided the final report in June 2020 [29]. While the data was still limited to draw general conclusions, no additional concerns were reported, 3 deaths in adult patients with TSC and everolimus were not attributed to the medication and no novel concerns were raised, regarding the long-term use of the mTOR inhibitor everolimus. There is no systematic data available, that assessed the impact of the therapeutic range to the long-term tolerability of sirolimus in neonates and young infants.

Taking into account this body of evidence from the literature, including work from others and our group [27, 28], two clinical trials in the United States (ClinicalTrials.gov: NCT05104983) and Poland (ClinicalTrials.gov: NCT04987463) are currently evaluating whether infantile-onset sirolimus treatment can prevent/delay seizure onset in TSC, using a very similar study design.

### 1.3.9 COVID-19 related risks

The current COVID-19 pandemic is not expected to bring any additional risks to the study. Participants in the treatment group will need to visit the outpatient clinic more frequently during the 6-week dosing phase, compared to SOC. However, these visits cannot be carried out over the telephone as a physical examination and the collection of blood samples are required. While the study medication may have possible immunosuppressive effects, particularly at higher doses, study results in elderly patients suggest a possible protective effect with respect to SARS-CoV-2 infections at lower doses [51]. The impact of the medication on the risk of acquiring COVID-19 in infants and young children is yet to be determined.

### 1.3.10 Individual risk-benefit evaluations

In order to continuously monitor risk-benefit ratios of participants in the treatment group, the following procedures are implemented into the study visits:

1. At each study site, two subinvestigators with clinical experience in the treatment of children with TSC will evaluate the individual risk-benefit profile of the participants treated with the IMP at 6, 12, and 18 months of life, considering the individual IMP pharmacovigilance as well as possible novel findings in the research field being considered as relevant for the respective individual. These evaluations are implemented into the study visits V6, V8, and V10. If one of the evaluating pediatricians comes to the decision that the respective participant is unlikely to benefit from continuation of IMP application, the treatment will be terminated. The participant will be continued receiving SOC and will be followed-up until the primary endpoint of the study. The results from each risk-benefit evaluation will be documented in the eCRF and on a separate, signed worksheet at the respective study visit. All decisions will be reported to the coordinating investigator.
2. For independent supervision of the process, risk-benefit evaluations of the study sites will also be assessed by the DSMB within the scope of the regular meetings to minimize assessment bias risk at the study sites and to identify participants-at-risk with a comparable safety profile.
3. The coordinating investigator will continuously secure implementing novel knowledge on early prognostic factors that help to assess the individual child's risk for abnormal neurodevelopment as well as current knowledge on the risk profile of the IMP in infants. Novel findings will be shared and discussed with the Scientific Advisory Board and additionally with the DSMB and the other investigators in a timely manner.

**Figure 2: Workflow Risk-Benefit-Evaluation**

[figure not shown]

|                                                                    |                                              |                                |
|--------------------------------------------------------------------|----------------------------------------------|--------------------------------|
| Clinical Trial Code: PROTECT
EU trial number: 2022-502332-39-00 | Trial Protocol
(Version 06; (01.10.2024)) | Page 35 of 110
CONFIDENTIAL |
|--------------------------------------------------------------------|----------------------------------------------|--------------------------------|

## 2. Clinical Trial Objectives and Endpoints

### 2.1 Primary Objective and Primary Endpoint

The aim of this trial is to reduce neuropsychologic impairment in tuberous sclerosis patients by restoring disrupted mTOR signaling by early preventive addition of the mTOR inhibitor sirolimus to SOC. The primary endpoint is the **neuropsychologic outcome at 24 months of age assessed by rater blinded neuropsychologic testing measured by the cognitive scale on the Bayley Scales of Infant and Toddler Development III (BSID-III) compared with SOC alone.**

### 2.2 Secondary Objectives and Endpoints

#### 2.2.1 Main Trial

The secondary objectives are adapted to the purpose of this study from the EPISTOP trial, a phase IIb study evaluating the impact of early versus late preventive treatment with vigabatrin on epilepsy in infants with TSC at 2 years of age [14] and will be compared between intervention and control groups:

1. Neuropsychologic outcome at 12 months of age assessed by rater blinded neuropsychologic testing using the cognitive scale on the BSID-III in both groups. Cognitive impairment will be defined as BSID-III cognitive scale score <70 similar to the EPISTOP trial [14].
2. Adaptive behaviour assessed by the Vineland Adaptive Behaviour Scales (VABS-3; digital) at the age of 12 months and 24 months.
3. Evidence for autism spectrum disorder measured at 12 months and 24 months of age by the Autism Diagnostic Observation Schedule (ADOS-2). Suspicion of autism spectrum disorder will be defined as ADOS > 12, similar to the EPISTOP trial [14].
4. Evidence for autism spectrum disorder measured by the Modified Checklist for Autism in Toddlers revised (M-CHAT-R/F).
5. TSC-associated Neuropsychiatric Disorders (TAND) severity assessed by the TAND-L Checklist (German version) at 12 and 24 months.
6. Assessment of seizure frequency and the occurrence/severity of Infantile Spasm measured by seizure diaries, caregiver questionnaires and EEG recordings.
7. Reduction of number and size of cardiac rhabdomyoma and arrhythmia (if present).
8. Reduction of cerebral tumor number and size on cMRI (if present).
9. Adverse events (AE), serious adverse events (SAE) and Adverse Events of Special Interest (AESI), assessed by the *Common Terminology Criteria of Adverse Events (CTCAE, Version 5.0)*.
10. Assessment of laboratory data and vital signs.
11. Assessment of EEG recordings for the occurrence of hypsarrhythmia and epileptiform discharges.
12. Renal changes in abdominal sonography: Volume and size of angiomyolipomas (if present), kidney size, renal pelvis dilation, echogenicity.

|                                                                    |                                              |                                |
|--------------------------------------------------------------------|----------------------------------------------|--------------------------------|
| Clinical Trial Code: PROTECT
EU trial number: 2022-502332-39-00 | Trial Protocol
(Version 06; (01.10.2024)) | Page 36 of 110
CONFIDENTIAL |
|--------------------------------------------------------------------|----------------------------------------------|--------------------------------|

## 2.2.2 Accompanying Research

Several accompanying studies will evaluate:

1. Genetic profiling of patient-derived biomaterial to identify predictors for treatment response and TSC-associated complications.
2. Assessment of response to vaccinations under treatment with IMP compared to SOC.
3. Neuropsychological follow-up of children with tuberous sclerosis treated preventively with mTOR inhibitors at 60 months of age measured by the Vineland Adaptive Behaviour Scales (VABS-3; digital), the Social Communication Questionnaire (SCQ, German version), the TAND-L Checklist (German version) and Health-related quality of life measured by the Quality of Life in Childhood Epilepsy (QOLCE) questionnaire.

### Project 1. Genetic profiling approach to identify individual predictors for treatment response and TSC-associated complications

TSC is highly variable in age at onset, disease severity, presence of core symptoms and occurrence of TSC-associated complications, even for patients of the same genotype [52]. Differences in genetic modifier genes and gene expression signatures (transcriptomics) may account for this heterogeneity. Analyses of genetic and transcriptomic profiles have been successfully used to identify risk profiles for TSC-associated cerebral and renal malformations [53, 54]. By using an unbiased genomic/transcriptomic approach, we aim to establish personalized disease profiles and identify predictors for individual trajectories and treatment responses. Ultimately, these results hold the potential to inform on patient stratification and tailoring of personalized treatment approaches.

Possible applications to identify subgroups are:

1. Genomics: Exome/Genome sequencing to identify shared genetic modifiers predisposing for/protective of TSC-associated manifestations and response to the study medication.
2. Epigenetics: Analysis of methylation profiles to identify epigenetic signatures correlating with disease outcomes and longitudinal changes under therapy.
3. Transcriptomics: mRNA-Sequencing to identify up-/down-regulated genes/pathways and correlations with disease outcomes and their longitudinal changes under therapy with the study medication.

This approach can broaden the understanding of disease mechanisms and increase the accuracy of predictions.

To allow a detailed analysis of our cohort, standardized sample collection will be done longitudinally at two timepoints:

- Screening: DNA, RNA
- Visit 12 (24 months of age): DNA, RNA

Blood for DNA (~1ml) and RNA (~2,7ml), will be collected during venous blood sampling procedures necessary to determine safety and efficacy of the study medication (intervention group) or establishment of the control group (non-intervention group). Since the total amount of required blood might be too high for neonates and infants, not all studies will be conducted for each individual. Blood sampling for DNA can be delayed to a future visit if not collected at screening, since changes to the DNA are not expected to occur under therapy.

|                                                                    |                                              |                                |
|--------------------------------------------------------------------|----------------------------------------------|--------------------------------|
| Clinical Trial Code: PROTECT
EU trial number: 2022-502332-39-00 | Trial Protocol
(Version 06; (01.10.2024)) | Page 37 of 110
CONFIDENTIAL |
|--------------------------------------------------------------------|----------------------------------------------|--------------------------------|

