#### Accompanying research:

- RNA samples will be collected for accompanying research at screening and 24 months (V12) (PAXgene® Blood RNA System, 2,7ml).
- DNA samples will be collected for accompanying research at 24 months (V12) of age.

|                                                                    |                                              |                                |
|--------------------------------------------------------------------|----------------------------------------------|--------------------------------|
| Clinical Trial Code: PROTECT
EU trial number: 2022-502332-39-00 | Trial Protocol
(Version 06; (01.10.2024)) | Page 79 of 110
CONFIDENTIAL |
|--------------------------------------------------------------------|----------------------------------------------|--------------------------------|

- Vaccination titres: the titers of vaccines applied during the first year (measles, mumps, rubella, tetanus, pertussis, varicella) will be assessed in both groups.

Special tubes, packaging and labels will be provided by the sponsor or his delegate(s). After sample collection, probes will be labelled and send immediately to the Institute of human genetics Leipzig for RNA and DNA, according to the investigator's manual provided by the sponsor or his delegate(s).

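### Project 1 lets the first DNA sample slip past the first dose for a reason that covers DNA sequence but not methylation, and section 6.8 omits the screening DNA sample

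*Protocol*

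**What the plan says.** Section 2.2.2, Project 1, names three possible uses of the biomaterial: genomics, epigenetics and transcriptomics. The epigenetic item reads "Analysis of methylation profiles to identify epigenetic signatures correlating with disease outcomes and longitudinal changes under therapy". Two collection points follow: "Screening: DNA, RNA" and "Visit 12 (24 months of age): DNA, RNA".

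The section then adds an exception for DNA alone: "Blood sampling for DNA can be delayed to a future visit if not collected at screening". The reason given is "since changes to the DNA are not expected to occur under therapy". No limit is set relative to the first dose, and no type of analysis is excluded from the permission.

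Table 1 agrees with the two planned points: optional DNA is marked for all participants at screening and for both arms at V12. The accompanying-research list in section 6.8 does not agree: "DNA samples will be collected for accompanying research at 24 months (V12) of age". The RNA line directly above it gives both screening and V12.

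**The concern.** The exception and the aim sit in the same section and pull against each other. A germline sequence is the same whenever it is read, so a late sample costs the genomics item nothing. Methylation is measured here because it may change during treatment. A first sample taken after the drug has started is not a baseline for that question.

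The mismatch in 6.8 adds a second route to the same loss. A site working from that list would draw DNA once, at 24 months, and would have no first value to compare with.

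What is at stake is the interpretability of one exploratory analysis. The loss cannot be undone later, because no analysis document can recover a pre-dose sample that was never drawn.

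**Working it through.** The protocol gives no figure for this point, so there is none to reproduce. The check sets the places side by side and then works out when a delayed sample would fall.

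**1. DNA time points by source**

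| Source | Screening | V12 (24 months) |
|---|---|---|
| 2.2.2, Project 1 | yes, may be delayed | yes |
| Table 1 | yes (optional) | yes (optional) |
| 6.8, accompanying research | not listed | yes |

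RNA appears at both points in all three places and is not covered by the delay rule.

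**2. What each route leaves for one child**

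- Sampled at screening: two DNA samples, the first before treatment. Within-child change is measurable.
- Treated child, first sample delayed past first dose: two samples at most, none before treatment.
- Control child, first sample delayed: no drug exposure, but an older age at the first sample.
- 6.8 followed literally: one sample, so no change can be computed.

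**3. When a delayed sample would fall**

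Section 2.2.2 ties the collection to other sampling: "Blood for DNA (~1ml) and RNA (~2,7ml), will be collected during venous blood sampling procedures". I therefore assume that a missed sample is taken at the next scheduled laboratory draw. Table 1 has no haematology or chemistry at V1. The next draw is:

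- treatment arm: V2, day 14 ± 4, that is 14 − 4 = 10 to 14 + 4 = 18 days after the first dose;
- control arm: V6, at 6 months of age. Enrolment is at 0 to <4 months, so the first sample moves by more than 6 − 4 = 2 months and by up to about 6 − 0 = 6 months.

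Section 6.5 places a control laboratory examination at week 0 (V1). Screening and V1 may fall on one day, so this can be the screening draw itself; Table 1 gives no separate one.

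The interval from a delayed first sample to V12 would then also differ by arm:

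- controls: 24 − 6 = 18 months;
- treated, taking 14 days as 0.5 month: from just over 24 − 4 − 0.5 = 19.5 months to 24 − 0 − 0.5 = 23.5 months.

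So delayed first samples differ between arms in drug exposure, and in age and follow-up interval as well. These are the earliest dates under the assumption; the permission itself allows any later visit.

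**4. Is delay plausible?**

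Section 2.2.2 expects that the blood required may be too much for neonates and infants. DNA plus RNA is 1 + 2.7 = 3.7 ml. Section 1.3.4 says that research-related blood loss should not exceed 1% of blood volume at any time, so 3.7 ml needs 3.7 / 0.01 = 370 ml of blood volume. Assuming 80 to 90 ml/kg (not in the protocol), that is 370 / 90 = 4.1 kg to 370 / 80 = 4.6 kg. Below that weight the two samples together would exceed the cap.

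DNA alone needs only 1 / 0.01 = 100 ml, or 100 / 90 = 1.1 kg to 100 / 80 = 1.25 kg, before any other research blood taken at the same time. Delay is therefore plausible where both samples are wanted from a small infant, but not inevitable.

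**The case against.** The strongest reply is that the plan is sound when followed. Table 1 and 2.2.2 both schedule DNA at screening; delay is an exception. Section 6 opens by saying that it describes procedures as set out in the schedule of assessments, so the 6.8 line is most likely an editorial slip that the schedule would override. Methylation is one of several possible applications in optional, separately consented research. Section 9.5.2 leaves those analyses to a separate description, and 11.2 requires an analysis plan for stored samples. A rule on which children enter the longitudinal analysis could sit there, and 2.2.2 already accepts that not every study will be done in every child.

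Much of this stands. A reader might infer that within-child methylation change cannot be measured at all, or that none of the up to 60 children would have a baseline. The documents do not support either. Children sampled at screening have a valid first value, and a total loss would require every site to follow 6.8 against both Table 1 and 2.2.2. A reader might also infer that the delayed comparison is biased towards no change. The direction cannot be derived: a late first sample drops early developmental change as well as early drug effect, and does so differently in the two arms.

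Two things do not yield to the reply. The stated reason for the delay is wrong for methylation whatever a later analysis plan says. And a later plan can exclude children without a pre-dose sample, but it cannot supply the sample.

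**Conclusion.** Wrong as written, and minor. The delay permission rests on a reason that does not cover the methylation aim in the same section, and 6.8 leaves out a sample that Table 1 and 2.2.2 schedule. Within-child methylation change under therapy is measurable only in children whose first DNA sample precedes the first dose.

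The number affected is unknown, because the protocol gives no expected rate of delay. The V2 and V6 timings rest on the assumption that a missed sample is taken at the next scheduled laboratory draw in Table 1. The weight range rests on an assumed 80 to 90 ml/kg.

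The point should not be read as touching the main trial. No primary, secondary or safety analysis uses methylation, and the RNA plan is unaffected.

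**What to change.** - In 6.8, list DNA at screening and V12, as Table 1 and 2.2.2 do.
- In 2.2.2, limit the delay permission to sequence analyses.
- Restrict the longitudinal methylation analysis to children with a DNA sample before the first dose (controls: by V1), and report by arm how many qualify. The permission in 2.2.2 should state this condition; the detail can go into the separate plan for the accompanying research.

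The changes are wording. They add no visit and no blood beyond what Table 1 already schedules. The downside is fewer children in this exploratory analysis where an early sample is not possible. The changes to collection help only children not yet enrolled, so they are worth making while recruitment is open.
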